## Abstract

**Background::**

Atopic dermatitis (AD, atopic eczema) is a pruritic, inflammatory, chronic skin disease. Since there is limitation of conventional treatment of AD, traditional herbal medicine can be an attractive therapeutic option in patients having AD for a long time. So-Cheong-Ryong-Tang (SCRT) has been found to inhibit histamine release and degranulation of mast cells, differentiation of basophils, and proliferation of eosinophils. We designed this clinical trial to evaluate the efficacy and safety of SCRT as compared to placebo in patients with AD and respiratory disorders.

**Methods/design::**

This study is a single-center, randomized, double-blind, placebo-controlled, and investigator-initiated clinical trial. A total of 60 patients between 7 and 65 years of age with AD and respiratory disorders who received a diagnosis of AD by Hanifin and Rajka criteria who scored 15 to 50 in a scoring atopic dermatitis (SCORAD) will be enrolled. Participants will be randomly assigned to the SCRT or placebo group in a ratio of 1:1 and they will have a visit schedule comprising 4 visits including a screening visit during 8 to 10 weeks. The participants will be administered SCRT or placebo 3 times a day for 4 weeks. The primary outcome will be measured by a change of the SCORAD index. The secondary outcomes will be measured by changes in the dose and frequency of usage of the AD ointment, dermatology life quality index scores, pruritus and sleep disorder in visual analog scale, skin moisture content, skin surface temperature, Hamilton anxiety rating scale scores, depression rating scale scores, stress/autonomic nervous function test, and attention deficit hyperactivity disorder survey scores at week 4 as compared to those at the baseline.

**Discussion::**

To the best of our knowledge, SCRT has rarely been reported for dermatologic diseases. This will be the first clinical trial to assess the efficacy and safety of SCRT in patients with AD and respiratory disorders. We hope that the results of this trial will provide evidence for the use of SCRT as a new treatment for AD with respiratory disorders.

**Trial registration::**

Korean National Clinical Trial Registry, Clinical Research Information Service. (KCT0004148) (https://cris.nih.go.kr/cris/search/search_result_st01_en.jsp?seq=14981<ype=&rtype=).

## Introduction

1

Atopic dermatitis (AD, atopic eczema) is a pruritic, inflammatory, chronic skin disease affecting up to 20% of children and 2% to 8% of adults in a majority of the countries worldwide.^[1]^ Although the prevalence of AD varies across countries, it is increasing both in the industrialized and low-income countries.^[2]^ Family history of atopic disorders including rhinitis and asthma is an important risk factor for the development of AD.^[3]^ Moreover, AD in infancy can progress to the development of asthma and allergic rhinitis, and this sequence is called the atopic march.^[4]^ The pathogenesis of AD is not completely understood; however, it is generally accepted that dysfunction of the skin barrier and hyper-immune activation are related to the onset of the disease.^[5]^ In the acute phase of AD, increased IgE production and eosinophilia are observed and are associated with increased expression of TH2 cytokines, interleukin (IL)-4, IL-5, and IL-13.^[6]^

The optimal treatment of AD consists of avoiding triggering factors, maintenance of skin hydration, restoration of the skin barrier function, patient education, and pharmacologic options, such as topical corticosteroids, and topical calcineurin inhibitors.^[7]^ However, long term use of systemic corticosteroids can result in severe adverse effects, such as hypothalamic-pituitary-adrenal axis suppression, growth suppression in children, osteoporosis, glucose intolerance, Cushing syndrome, opportunistic infections, and rebound flaring.^[8]^ Further, some patients remain unresponsive to conventional treatment.

Traditional herbal medicine (THM) has been widely used in East Asian countries for thousands of years to treat various diseases.^[9]^ For the treatment of AD, 74% of patients in Korea have used THM as an alternative therapy.^[10]^ THM can be an attractive therapeutic option in patients having AD for a long time. So-Cheong-Ryong-Tang (SCRT, Xiao-Qing-Long-Tang in China or Sho-Seiryu-To in Japan) is the mixture of the following 8 herbs: *Epoedrae Herba*, *Paeoniae Radix* Alba, *Schizandrae Fructus*, *Pinelliae Rhizoma*, *Asari Herba Cum Radice*, *Zingiberis Rhizoma*, *Cinnamomi Ramulus*, and *Glycyrrhizae Radix*.^[11]^ SCRT has been used clinically for the treatment of various respiratory diseases, such as allergic rhinitis, bronchial asthma, and common cold.^[12]^

SCRT has been found to inhibit histamine release and degranulation of mast cells,^[13]^ differentiation of basophils,^[14]^ and proliferation of eosinophils.^[15]^ Furthermore, it is reported that SCRT regulates Th1/Th2 immune activity under Th2 dominant condition.^[16]^ To the best of our knowledge, SCRT has rarely been reported for dermatologic diseases, except for a case report and a clinical trial that studied the efficacy of SCRT in conjunction with electrical stimulation in patients with AD.^[17,18]^ However, no studies have evaluated the effects of SCRT monotherapy in patients with AD and respiratory disorders. Hence, we designed this trial to evaluate the efficacy and safety of SCRT as compared to placebo in patients with AD and respiratory disorders.

## Methods

2

### Study design

2.1

This study was designed as an investigator-initiated, double-blind, randomized, placebo-controlled clinical trial to assess the efficacy and safety of SCRT in patients with AD and respiratory symptoms. A total of 60 participants will be divided into an SCRT group and a placebo group at a 1:1 ratio and the study drugs will be administered for 4 weeks. At weeks 4 and 8 of follow-up, the participants will visit the study institute and be assessed the efficacy and safety (including the onset of adverse events). Specific schedules and investigations are summarized in Table 1 and Figure 1. The protocol (version 1.1) follows standard protocol items: recommendation for interventional trials guideline.

**Table 1 T1:**
[figure not shown]
Schedule of enrolment, interventions, and assessments.

**Figure 1 F1:**
[figure not shown]
Study flowchart describing the details of the randomized controlled trial. The entire trial includes assessments on week 1, week 4, and week 8 (follow-up visit).

### Participants

2.2

#### Recruitment

2.2.1

The participants are expected to be recruited through the Wonkwang University Oriental Medical Hospital at Iksan from June 2019 to August 2020. Advertisement for participating in the study will be put up on the bulletin boards of the hospital, city, shopping complexes, and apartments. During the screening, the investigators will explain all the necessary information related to the trial and predictable outcomes to the participants and their guardians and obtain their signatures on the consent form. The participants can withdraw from the study at any time without any problem. The written consent contains the study background, objective, investigational drugs and placebo, expected results, and predicted benefits and harms.

#### Inclusion criteria

2.2.2

The subjects of this study should meet all the following criteria:

(1)Male and female patients between 7 and 65 years of age, scoring 15 to 50 in a scoring atopic dermatitis (SCORAD), and having more than 3 of major criteria and 3 of minor criteria based on the Hanifin and Rajka diagnostic criteria(2)Patients marking more than 1 respiratory disease and symptoms in the questionnaire survey for respiratory disorders(3)Those who fully understand our study after detailed explanation, and voluntarily agree to participate and provide written consent to undertake precautions (in case of a child, both the child and the parent should sign the consent form)

#### Exclusion criteria

2.2.3

(1)Patients undergoing intensive drug treatment for severe AD (antihistamine, adrenocortical hormone, herbal drugs, etc)(2)Patients using an oral antihistamine, steroid, antibiotic, systemic photochemotherapy, or another immunosuppressant within 4 weeks before initiation of the trial(3)Patients with systemic infection or undergoing systemic antibiotic treatment(4)Patients with a skin disease other than AD, pigmentation, or a large scar around the AD site(5)Patients taking interferon drugs (interferon-alpha, interferon-beta, etc)(6)Patients with liver diseases, such as cirrhosis and liver cancer(7)Patients with a platelet count of <100,000/mm^3^ due to liver dysfunction caused by chronic hepatitis(8)Patients with kidney diseases, such as acute/chronic renal failure, and nephrotic syndrome(9)Patients with acute severe cardiovascular diseases, such as heart failure, myocardial infarction, and stroke(10)Patients with chronic diseases, such as uncontrolled hypertension, diabetes, gastrointestinal disorder, hyperhidrosis, and dysuria(11)Patients taking potassium-containing drugs, licorice-containing drugs, glycyrrhizinate or its salt-containing drugs, loop diuretics (furosemide, ethacrynic acid), or thiazide diuretics (trichloromethiazide) within 4 weeks before initiation of the trial(12)Patients taking ephedra or ephedrine-containing drugs, monoamine oxidase inhibitors, drugs for thyroid disorders, catecholamines, or xanthine drugs within 4 weeks before initiation of the trial(13)Patients taking antipsychotic drugs within 2 months before screening(14)Patients who participated in any other clinical trial within the preceding 4 weeks(15)Patients with previous hypersensitivity reaction to our investigational drug or its components(16)Patients with a history of drug or alcohol abuse(17)Women who are pregnant or lactating(18)Among fertile women with a chance of being pregnant, those who do not practice proper contraception (excluding women who underwent surgical sterilization)(19)Patients with thyroid disorders with thyroid-stimulating hormone (TSH) level is ≤0.35 μU/mL or ≥4.94 μU/mL at screening(20)Patients determined to be unsuitable for participating in this study by the principal investigator due to the results of the diagnostic tests or any other reasons.

### Study phase

2.3

During screening at the hospital, the eligibility of the participants will be adjudicated based on their medical history, medication history, results of blood and urine tests, vital signs, SCORAD index, and Hanifin and Rajka diagnostic criteria. Then the participants determined to be eligible for the trial will visit the hospital (visit 1) within 2 weeks after screening and will be randomly assigned to the treatment or the control group. After group allocation, various surveys including AD survey and physical examination will be conducted, and the participants will be administered with the investigational drug 3 times a day for 4 weeks. After 4 weeks, the participants will be asked to visit the hospital again (visit 2) and undertake the same surveys, examinations, and blood investigations as those at visit 1. For the next 4 weeks, all drugs will be withdrawn except Lacticare, a concomitant drug, and the participants will be asked to visit the hospital (visit 3) and undertake the same surveys and investigations. The specific schedules and types of examinations are summarized in Table 1.

### Intervention

2.4

Experimental group and control group will be orally administered 1 packet of either SCRT or placebo 3 times a day before meals for 4 weeks. Based on the adult dosage of commercial SCRT extract granule (3 g thrice daily), the dose was set as 9.0 g/d for patients of 15 to 65 years of age. The dose in patients between 7 and 14 years of age was set as 6.0 g/d (two-third of the adult dosage) based on the Oriental and Herbal Medicine Pharmaceutical Approval Article 16 Usage and Dose No. 7. SCRT and placebo are brown granules of the same color, dosage form, and physical property. The ingredients of each drug are shown in the Table 2. The manufacturer of the drugs is Hanpoong Pharm ([name]). The drugs will be stored in an airtight container at room temperature (1–30°C). The concomitant medication for the experimental and control groups is hydrocortisone acetate 1%/Lacticare ointment (100 g of the ointment contains 1.0 g of the main ingredient hydrocortisone, 0.15 g of methyl ρ-hydroxybenzoate, and 0.05 g of propyl ρ-hydroxybenzoate) which can be used during the trial period of 8 weeks. The participants will record the number of drug administration and the corresponding dosage.

**Table 2 T2:**
[figure not shown]
Composition of So-Cheong-Ryong-Tang and placebo.

#### Concomitant medications

2.4.1

(1)Product (code) name and manufacturer: Lacticare HC lotion 1% (hydrocortisone), Korean Pharma Inc,(2)Dosage form and property: white lotion.

### Randomization

2.5

The participants who are willing to provide written consent to participate in this trial will be given a screening number according to the order of their written consent. The participants determined to be eligible for the trial following the inclusion and exclusion criteria will be randomly assigned a number in the order of their visit dates, and the treatment for each participant will be prescribed according to the random code generated. For randomization, block randomization will be used with block sizes of 4, 6, or 8 with a set ratio of 1:1. After generating the randomization table, drugs for each patient will be packaged according to the table, labeled according to the randomization code, and transported to the pharmacist manager or herb pharmacist in the clinical trial research institute. Then, the pharmacist manager or herb pharmacist will dispense the drugs after matching the randomization codes to participants.

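### Randomisation names no stratification by the trial's own age/dose groups (7-14 and 15-65 years), and age is not a prespecified covariate

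*Protocol article*

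**What the plan says.** **Randomisation (protocol article, section 2.5).** The method is that "block randomization will be used with block sizes of 4, 6, or 8 with a set ratio of 1:1". Eligible participants "will be randomly assigned a number in the order of their visit dates". No stratification factor and no separate list by age is mentioned.

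**Packing and dispensing (section 2.5).** "After generating the randomization table, drugs for each patient will be packaged according to the table, labeled according to the randomization code". The pharmacist then "will dispense the drugs after matching the randomization codes to participants". No step involving age or dose is described.

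**Dose (section 2.4).** Both arms "will be orally administered 1 packet of either SCRT or placebo 3 times a day before meals for 4 weeks". The daily dose is 9.0 g for ages 15 to 65. For the younger group, "The dose in patients between 7 and 14 years of age was set as 6.0 g/d", given as two thirds of the adult amount.

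**Population (sections 2.1, 2.2.2 and Discussion).** Sixty participants aged 7 to 65 are planned. The Discussion says that adults are included here, unlike in the previous study. No quota or expected share of either age group is given.

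**Adjustment (section 2.10).** Week-4 changes are compared by independent t test. An analysis of covariance is also described, using the baseline value of each outcome and those demographic variables that turn out to be non-homogeneous. Age is not named.

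**The concern.** The trial spans ages 7 to 65 and splits that range into two dose groups. That makes age group the natural factor to balance. The secondary outcomes include quality of life, anxiety, depression and attention-deficit scales (section 2.8.2), on which children and adults may plausibly differ, although the article does not discuss this.

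With about 30 participants per arm, balance on age is left to chance. Blocks of 4, 6 or 8 keep the arm totals equal but do nothing for the age mix within them. If age group is related to the change in SCORAD, an uneven split adds noise to the unadjusted comparison and may shift the observed difference in a given trial. The planned response depends on whether the imbalance is judged large enough after the fact, so the primary model is not fixed in advance.

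A second, separate matter is that the article does not explain how packs made up by randomisation code carry two age-dependent daily doses under a single packet rule.

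**Working it through.** **1. The plan's own figures.** Dose: 3 g × 3 = 9.0 g/d, and 2/3 × 9.0 = 6.0 g/d, as stated. Sample size (section 2.7): the difference is 13.8 − 7.9 = 5.9, the SD is 8.2 and power is 80%. A one-sided 5% test gives n = 2 × [8.2 × (1.645 + 0.842)/5.9]² ≈ 23.9, so 24 per group, and 24/0.8 = 30, as stated. (A two-sided 5% test would give 31, or 39 after dropout. That is a different question.) Nothing here disputes or changes the 30 per group.

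**2. Chance imbalance with no stratification.** Inputs are 60 participants at 1:1 (section 2.1), so 30 per arm, and a share p aged 7-14. The documents give no p, so 20%, 30% and 50% are assumed.

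If age group is independent of list position, the number of children in each arm is approximately binomial(30, p). The between-arm difference in counts then has

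SD = √(2 × 30 × p × (1 − p)).

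| Assumed share aged 7-14 | SD of difference | P(differ by ≥ 4) | P(differ by ≥ 6) |
|---|---|---|---|
| 20% | √9.6 = 3.1 | 26% | 8% |
| 30% | √12.6 = 3.5 | 32% | 12% |
| 50% | √15 = 3.9 | 37% | 16% |

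The probabilities come from 20,000 simulated lists of 60 with random permuted blocks of 4, 6 and 8. The exact distribution of the difference between two binomial(30, p) counts agrees to within one percentage point (25.6%, 32.3%, 36.6% for ≥ 4; 7.5%, 12.0%, 15.5% for ≥ 6).

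**3. Sensitivity to the calculation.** If the total number of children K is fixed, the hypergeometric distribution applies. K = 20, 24 and 30 give 41%, 43% and 44% for a difference of 4 or more. These values are high because an even K allows only even differences. Odd K gives 28% to 30% (K = 21, 25, 29), and K = 12 gives 33%. Treating K as random, as in step 2, averages over this and is the fairer summary.

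**4. With stratified blocks.** Within one stratum only the last, incomplete block can be unbalanced. The largest possible difference is half the largest block, 8/2 = 4. Simulating strata of 12, 18 and 30 children gives a difference of 4 in 0.3% to 0.4% of lists and never 6. N remains 60.

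**5. What an imbalance could do to the primary result.** A difference of 4 children is 4/30 = 13 percentage points. If children and adults differed in mean SCORAD change by 2 to 5 points (an assumption), the observed difference would shift by 0.133 × 2 ≈ 0.3 to 0.133 × 5 ≈ 0.7 points. The planned difference is 5.9, and its standard error with 30 per arm is 8.2 × √(2/30) ≈ 2.1. The shift is modest.

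**6. Packets and doses side by side.** At three packets a day, section 2.4 implies 9.0/3 = 3 g per packet for ages 15-65 and 6.0/3 = 2 g for ages 7-14. Section 2.5 describes packs made from the table, labelled by code and dispensed by code, with no mention of age. Neither section says how the two fit together.

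**The case against.** Several points on the other side are sound.

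- **No bias.** A reader might infer that the design confounds treatment with age or dose. It does not. The age rule applies equally to active drug and placebo, and imbalance under 1:1 randomisation is by chance. What remains is a loss of precision and a possible distortion of the single observed result.
- **Adjustment exists.** Section 2.10 does provide an ANCOVA, and a marked age imbalance could enter it. This softens the concern but does not remove it, because the covariate is included only if it looks uneven.
- **Accepted practice.** Unstratified blocks with covariate adjustment are a legitimate design for a 60-patient single-centre trial. This is an improvement on offer, not an error.
- **Small effect on SCORAD.** Under the assumptions in step 5 the shift is under 1 point. No large effect on the primary outcome has been shown.
- **Inference from silence.** The article nowhere uses the word unstratified. That reading rests on one table, one visit-date sequence and no named factor, in an article that condenses a fuller protocol.

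A reader might also infer that sections 2.4 and 2.5 contradict each other, with packs sealed before anyone's age is known. The text does not go that far. It places packing after the table is generated and says nothing about its timing relative to enrolment. Packs of both contents for each code, or code ranges by age, would fit the wording. Tables 1 and 2 are not visible here, and packaging detail may sit in the full protocol. The gap is real; a contradiction is not shown.

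**Conclusion.** The point holds as a worthwhile, inexpensive improvement. As described, the randomisation does not balance the two age/dose groups that the trial itself defines. With an assumed 20% to 50% of participants aged 7-14, there is roughly a one in four to better than one in three chance (26% to 37%) that the arms differ by 4 or more children, and an 8% to 16% chance of 6 or more. The consequence is lost precision and a less secure observed comparison, not bias. The planned remedy is weaker than it need be, because the covariates depend on the imbalance observed.

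The result rests on the assumed share of children, on age group being independent of list position, and on reading section 2.5 as a single unstratified sequence.

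The packet question is secondary. Sections 2.4 and 2.5 leave it open and need to be reconciled; on its own it would be no more than missing detail.

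**What to change.** 1. In section 2.5, stratify the block randomisation by the existing age/dose groups (7-14 and 15-65 years), with a separate list and number series for each and 1:1 allocation within each.
2. In section 2.10, prespecify the primary analysis as an ANCOVA of week-4 SCORAD change on treatment, baseline SCORAD and age/dose stratum, whatever imbalance is observed. Remove the selection of covariates by observed non-homogeneity from the primary model.
3. Reconcile sections 2.4 and 2.5: state how code-labelled packs deliver the two stated daily doses under the one-packet-three-times-a-day rule, and how the blind in section 2.6 is kept at dispensing. No view is taken here on which dose or packet content is right.

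**Cost.** A second list and number series, some spare packs in each stratum and one extra covariate. The sample size stays at 60. The change is cheapest before packing begins. If the lists are already in use, item 2 can still be adopted before unblinding.

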### Blinding

2.6

To obtain scientific results from the clinical trial and to avoid bias, the investigators and participants will be double-blinded so that they will be unable to know the groups to which the individual participants are assigned. The double-blinding will be maintained unless any medical emergency occurs. The information regarding the assigned groups will be locked and will be divulged only during statistical analysis after the whole clinical trial process is completed. When the allocation code will be broken due to adverse events, it will be reported to the institutional review board and the client following the procedures of code-breaking.

### Sample size calculation

2.7

The primary objective of this investigator-initiated clinical trial is to demonstrate a larger reduction in the AD symptom in the experimental group than the placebo group after 4 weeks of treatment and to validate the efficacy of SCRT in AD-related respiratory symptoms. To calculate the sample size, we anticipated that the mean changes in SCORAD scores after 4 weeks was 13.8 (*μt*) in the SCRT group and 7.9 (*μc*) in the placebo group. The standard deviation (*σ*) between the SCRT and placebo groups was assumed to be 8.2. The type 2 error at a 5% significance level was set as 0.2 and the power of the test was maintained at 80%. Taking a 20% dropout rate into account and maintaining the 1:1 allocation ratio between the SCRT and placebo groups, the final sample size was 30 in each group.

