### Statistical analyses

2.9

Appropriate statistical tests will be performed according to the characteristic of the data, the number of associated variables and their correlations, and the state of distribution. Windows Strategic applications software will be used for analysis. At a significance level of 5% and power of 80%, 95% confidence interval will be reported for the differences in the results between the groups. Participants with results of at least 1 efficacy outcome after administration of the investigational drug after randomization will be included for efficacy assessment. In addition, all subjects who will receive the investigational drug at least once and visit the hospital will be included for the safety assessment. Chi-square test or Fisher exact test will be used for the discrete variables, and analysis of variance or Kruskal–Wallis test will be used for the continuous variables.

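### Thirty per group with 20% dropout does not give 80% power for the two-sided 5% comparison that the analysis sections imply; t-test power is about 68% with that dropout and 78% with none

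*Protocol article*

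**What the plan says.** Section 2.7 (Sample size calculation) gives a complete set of inputs. The expected mean changes in SCORAD at week 4 are "13.8 (*μt*) in the SCRT group and 7.9 (*μc*) in the placebo group", with a standard deviation of 8.2. On error rates it says: "The type 2 error at a 5% significance level was set as 0.2 and the power of the test was maintained at 80" per cent. It then allows for 20% dropout at 1:1 allocation and reports that "the final sample size was 30 in each group". The objective is worded with a direction: "to demonstrate a larger reduction in the AD symptom in the experimental group than the placebo group after 4 weeks of treatment".

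Section 2.9 (Statistical analyses) says: "At a significance level of 5% and power of 80%, 95% confidence interval will be reported for the differences in the results between the groups". Section 2.10 (Efficacy assessment) plans an independent t test for the between-group difference in week-4 change. It also mentions an analysis of covariance adjusting for the baseline value and for unbalanced demographic variables, and does not say which of the two is primary. The words one-sided and two-sided appear nowhere in the article.

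**The concern.** Every input needed to check the sample size is stated, so the result should be reproducible under the test that the plan describes. It is not. A 5% level reported with a 95% confidence interval for a difference corresponds to a two-sided 5% test; a one-sided 5% test corresponds to a 90% two-sided interval or a 95% one-sided bound. Under a two-sided 5% test, 30 per group is slightly too few even before any dropout, yet the article says that dropout is already included.

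At stake is how the primary SCORAD comparison will be read. If the effect is as assumed, a trial described as having a 20% chance of missing it would, with the t test and the planned dropout, have a chance of about 32%. A non-significant result would then be taken as stronger evidence against the treatment than the design can supply.

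**Working it through.** **Inputs** (section 2.7): difference δ = 13.8 − 7.9 = 5.9; σ = 8.2, taken as the common SD of the change; α = 0.05; power 0.80; dropout 20%; 1:1 allocation. Standardised difference 5.9/8.2 = 0.72, and (σ/δ)² = (8.2/5.9)² = 1.932.

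**Formula** (normal approximation): n per group = 2(z_α + z_β)²(σ/δ)², with z_β = 0.842; enrolled = n/(1 − 0.20).

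**Reproducing the stated 30**

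- One-sided 5% (z_α = 1.645): 2 × (1.645 + 0.842)² × 1.932 = 23.9, so 24 evaluable; 24/0.8 = 30. This matches the article.
- Two-sided 5% (z_α = 1.960): 2 × (1.960 + 0.842)² × 1.932 = 30.3, so 31 evaluable; 31/0.8 = 38.75, so 39. This does not match.
- Two-sided 5%, exact (noncentral) t: 32 evaluable; 32/0.8 = 40. This does not match.

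Multiplying by 1.2 instead of dividing by 0.8 does not rescue the two-sided case: 31 × 1.2 = 37.2, so 38.

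**Power of the planned design for the t test.** The noncentrality is δ/(σ√(2/n)).

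- n = 24: 5.9/(8.2 × √(2/24)) = 2.49 on 46 degrees of freedom.
- n = 30: 5.9/(8.2 × √(2/30)) = 2.79 on 58 degrees of freedom.

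| Evaluable per group | Two-sided 5%, t | Two-sided 5%, normal | One-sided 5%, t |
|---|---|---|---|
| 24 (20% dropout) | 68.4% | 70.3% | 79.1% |
| 30 (no dropout) | 78.2% | 79.6% | 86.6% |

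**Detectable difference.** With 24 evaluable per group, the difference detectable with 80% power (two-sided 5%, t) is about 6.8 points, against the 5.9 assumed.

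**ANCOVA.** The SD of the change is held at 8.2. Write k for the ratio of baseline SD to week-4 SD and ρ for the correlation between them. The week-4 SD is then 8.2/√(1 + k² − 2ρk), and the residual SD after baseline adjustment is that figure times √(1 − ρ²). With 24 per group and two-sided 5%:

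| k | ρ = 0.3 | ρ = 0.5 | ρ = 0.7 |
|---|---|---|---|
| 1.0 | 86% | 80% | 75% |
| 0.8 | 79% | 73% | 69% |
| 0.6 | 72% | 69% | 69% |

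Neither k nor ρ is given in the article; both are assumptions, shown only to indicate the spread.

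**The case against.** The strongest reply is that two-sidedness is an inference. The article never states it, the objective has a direction, and a one-sided 5% calculation gives exactly 30. That is fair as far as it goes: two-sided is the implied reading, not a declared one. But directional wording is usual for a superiority objective and does not declare a one-sided test, and a one-sided 5% test would not match the 95% interval in section 2.9. On either reading section 2.7 needs correcting.

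A reader might go further and infer that the sample size was in fact derived one-sided. The documents do not support that as a statement of fact: they mention neither 24 evaluable participants nor a one-sided calculation. Another origin is conceivable. The two-sided normal formula gives 30.3, which rounds to 30 if the dropout inflation was never applied. The text says dropout was included, so the one-sided route fits better, but only the sponsor can say.

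A reader might also infer that the trial's true power is 68%. That figure belongs to the unadjusted t test with exactly 20% loss. With less loss it rises towards 78%, and section 2.10 also plans a baseline-adjusted ANCOVA, which may do better. It does not follow that ANCOVA restores the stated 80%. Section 2.7 uses no baseline correlation, and the ANCOVA figures run from about 69% to 86% on assumptions that the article does not support. Entry is limited to SCORAD 15 to 50 (section 2.2.2), which could make the baseline spread narrower than that at week 4 and so favour the lower figures.

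That the article condenses a fuller protocol does not explain the mismatch, because the calculation and its result are both printed.

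**Conclusion.** The point holds conditionally. Sidedness is not stated. Under the two-sided 5% reading implied by sections 2.9 and 2.10, the stated inputs need 39 to 40 enrolled per group, so 30 is 9 to 10 short. The stated 80% overstates t-test power by about 12 percentage points with the planned dropout (68.4%) and by about 2 with none (78.2%).

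These figures rest on the article's own difference of 5.9 and on 8.2 being the common SD of the change. They do not establish how 30 was obtained, nor the power of an adjusted analysis.

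**What to change.** Keep 60 participants and amend section 2.7 to:

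- state that the primary test is two-sided at the 5% level, in line with the 95% interval in section 2.9;
- replace the 80% with t-test power of about 68% with 20% dropout (24 evaluable per group) to about 78% with none, for a difference of 5.9 and SD of 8.2;
- say how 30 per group was derived, as confirmed by the sponsor and not as reconstructed here.

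In section 2.10, name the baseline-adjusted ANCOVA already planned as the primary analysis, since it should be at least about as precise as the t test on change. Quote no ANCOVA power unless data support the baseline to week-4 correlation and the variances at both visits.

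The cost is wording and a less favourable stated power; no participants are added. If the sponsor wants 80% for the two-sided t test with 20% dropout, that takes 39 to 40 per group, or 78 to 80 in all: 18 to 20 more participants than planned.
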